**Fig. 1 Fig1:**
[figure not shown]
Participant flow through the study. DMRC = Defence Medical Rehabilitation Centre; IP = individualised (outpatient) programme; MDT = multidisciplinary team (residential); MIAC = multidisciplinary injury assessment clinic

i.
**Group 1- MDT residential intervention**. Participants will receive an intensive, 7-day residential (in-patient) intervention at DMRC Headley Court. The intervention will include group-based exercise, manual therapy, hydrotherapy and education. The intervention will be delivered by a multidisciplinary team comprising a consultant physician, physiotherapist (PT), occupational therapist (OT) and exercise rehabilitation instructor (ERI). The intervention is anchored by admission and discharge procedures at day one and day seven respectively. Participants will typically complete seven therapy sessions each day of 30–60 mins duration over the remaining 5 days. The sessions enhance social contacts through group-based feedback before and after treatment, and by promoting partner and group exercise [27].ii.
**Group 2- IP outpatient intervention**. Participants will receive 8 treatment sessions, delivered over 6-weeks, combined with a home-based exercise programme. The first and last treatment session will be 45–60 min in duration. The remainder will be 30 min. The intervention will include individualised exercise, manual therapy and individually tailored education/advice. This programme will be delivered as an outpatient service from DMRC and led by an experienced physiotherapist. The treatment session duration reflects a realistic treatment dosage in clinical practice and has been shown sufficient to allow all components of treatment to be carried out [28]. Delivering the intervention in this realistic setting is important to determine the likelihood of effectiveness of the intervention in everyday practice [29]. The home-based programme will initially comprise 3-sessions per week but can be adjusted by the physiotherapist in response to patient progress. The home-based exercise programme in this study will be restricted to 3-times per week based upon the limited available evidence from clinical trials in non-arthritic hip pain [30], and a compromise between addressing the clinical goals whilst optimising adherence [31]. The home-based programme will be tailored to the individual needs of the patient, and utilise self-monitoring by means of an exercise diary.

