A definition of rehabilitation based on the concepts of structure and process is frequently used when assessing the content of health care interventions [32]. In our study the therapeutic content (e.g., exercise, manual therapy, education, home-based programme) is the same for both study groups. However, the structure and process will differ significantly. The residential arm is group treatment delivered by a MDT in a residential setting over 7-days. The outpatient arm is physiotherapist led individual treatment delivered during a series of weekly appointments over 6-weeks. Therefore, the amount of direct therapist contact, hands-on physical therapy and instructions surrounding exercise adjustment and education will differ. A detailed description of the treatment methods is contained in Table 3 and Additional file 1.

Eligible patients will be invited to participate in the study and complete an informed consent form. Patients agreeing to participate will be informed of treatment group assignment and referral arrangements by a civilian member of the clinical team, and all necessary study documents will also be provided. Ineligible patients will receive an ongoing referral in accordance with the existing UK military best practice care pathway. Following consent, participants will be consecutively randomised into either the residential or outpatient group by an independent administrator not involved in recruitment, assessment or treatment of participants. Baseline testing will be conducted immediately prior to commencement of treatment. Participants will be reassessed on completion of treatment (1-week (MDT); 6-weeks (IP)), and again at 12-weeks (week 12). During the 12-week follow up period, all participants will be advised to continue with an unsupervised home exercise programme. A log book record of exercise participation will be maintained during this period, and participants will be asked to refrain from seeking other treatments during the study.

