Group exercise	Strengthening exercises, active range of motion exercises, functional balance drills, gait drills, progressive co-ordination drills, non-weight-bearing aerobic/endurance exercise, minor team games.	Restore strength of deep hip stabilisers, improve core strength, increase joint range of motion, improve balance and neuromotor control, improve muscle endurance, promote group cohesion and social support.	12 (30–45 min)
Individual physiotherapy^a^	Manual therapy techniques, muscle activation and timing patterns, active and passive range of motion exercises, advice on home-exercise, gait re-education training.	Improve quality and timing of movement, improve muscle strength, reduce pain, increase joint range of motion, induce relaxation, promote normal walking gait.	5 (30 min)
Hydrotherapy/swimming	Non weight-bearing aerobic exercise, strengthening exercises, active range of motion exercises, self-paced recreational swimming, progressive/assisted weight-bearing exercise and activity.	Improve muscle strength, improve aerobic capacity, increase joint range of motion, improve confidence in weight-bearing, induce relaxation, promote enjoyment and variety of treatment.	3 (60 min)
Individual occupational therapy^b^	Relaxation techniques, postural re-education, cognitive behavioural therapy (CBT) techniques, self-help coping strategies, pain management.	Induce relaxation, promote behavioural change, control pain, correct/improve poor posture.	3 (60 min)
Patient education	Coping with pain, benefits of exercise, joint protection, anatomy and pathology of hip pain, nutrition.	Activity modification, reduction of pain, promotes behavioural change, weight management, improve knowledge of treatment options, improve ability to relax, improve knowledge of self-help techniques.	2 (60 min)

^a^Exercise dosage, progression and intensity will be governed by the physiotherapist and tailored to the needs of each individual patient; ^b^Occupational therapy referrals will be individually prescribed to selected patients

**Table 3 Tab3:** Overview of Outpatient Individual Programme (IP Group) and Residential (MDT Group) Study Treatment Schedule

Outpatient (IP) Protocol	Residential (MDT) Programme
Session 1 (45–60 mins)^a^	Day 1
• Subjective and objective assessment (20–25 mins)	• Admission MDT clinic and baseline measures
• Patient education (5-mins)	Day 2
• 1–2 manual therapy techniques (5–10 mins)	• Group-based introduction to treatment goal 1

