## Discussion

Hip arthroscopy and non-surgical interventions such as the treatments offered by physiotherapists, are recommended in the management of non-arthritic FAI [1, 9].

However, despite the popularity and acceptance of residential MDT rehabilitation in the UK military, there are no studies presenting empirical data on the structure, process or efficacy of non-arthritic hip pain care. Given the interest in this model across the wider healthcare sector, there is an immediate need to test the efficacy of residential rehabilitation practice in a randomised trial to ensure all future patients receive rehabilitation in the optimal clinical setting.

This paper presents the protocol for a randomised controlled trial that will compare the effects of a residential MDT intervention with conventional outpatient care on pain and physical function in young non-arthritic hip pain patients. The study will be the first RCT to evaluate the structure and process of residential versus outpatient treatment options in young active adults with intra-articular, non-arthritic hip pain. The study design includes methodological elements to minimise the potential for bias including a power calculation, randomisation and intention-to-treat analysis. The primary and secondary outcomes are reliable and valid self-report measures of function and pain, quality of life, and physical capacity tests including dynamic postural control, walking and HROM.

Bennell et al. [5, 28] have previously employed a semi-structured treatment programme similar to the out-patient intervention in our study. These authors highlight that whilst this approach restricts individual tailoring of the programme, it reduces treatment variation thereby ensuring the intervention is accurately reported and replicated. We chose not to include a ‘no treatment’ control arm as natural recovery is unlikely to occur in participants reporting functional impairments and pain at baseline [28], and imposing natural recovery could be considered unethical.

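### The protocol says therapeutic content is the same in both arms but lists modalities for the residential arm only, so a difference cannot be credited to structure, process or setting alone

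*Protocol article*

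**What the plan says.** After describing the two groups, the Procedure section declares: "In our study the therapeutic content (e.g., exercise, manual therapy, education, home-based programme) is the same for both study groups". It then says that structure and process differ, and that the amount of therapist contact, hands-on therapy and instruction will therefore differ as well. The Discussion repeats this framing: "The study will be the first RCT to evaluate the structure and process of residential versus outpatient treatment options in young active adults". It also ties the trial to making sure future patients are rehabilitated in the best clinical setting.

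The descriptions of the two arms are not the same:

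- Residential arm (Procedure, Group 1): "The intervention will include group-based exercise, manual therapy, hydrotherapy and education".
- Outpatient arm (Procedure, Group 2): "The intervention will include individualised exercise, manual therapy and individually tailored education/advice".
- Table 2, residential arm only, hydrotherapy/swimming, 3 sessions of 60 min: "Non weight-bearing aerobic exercise, strengthening exercises, active range of motion exercises, self-paced recreational swimming, progressive/assisted weight-bearing exercise and activity".
- Table 2, residential arm only, individual occupational therapy, 3 sessions of 60 min: "Relaxation techniques, postural re-education, cognitive behavioural therapy (CBT) techniques, self-help coping strategies, pain management". A footnote limits this: "Occupational therapy referrals will be individually prescribed to selected patients".
- Table 2, residential education topics: "Coping with pain, benefits of exercise, joint protection, anatomy and pathology of hip pain, nutrition".

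The Interventions text puts an occupational therapist and a nutritionist on the residential team, while a physiotherapist administers the outpatient programme.

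**The concern.** If content really were equal, a difference at 12 weeks could be read as the effect of how and where the same treatment is delivered. The Procedure and Discussion sections invite that reading. With modalities added in one arm, the same difference could come partly from those modalities, which need not be tied to residential delivery.

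The additions bear on measured outcomes. Table 2 gives pain control as a goal of occupational therapy, and VAS pain is a primary outcome. It gives muscle strength and range of motion as goals of hydrotherapy, and both appear in the secondary hypotheses. Those hypotheses are argued from therapist contact, intensity and supervised classes, so a gain would naturally be credited to delivery. The Abstract says the sustainability of the residential pathway has been questioned, so a misattributed effect could mislead that decision.

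**Working it through.** The plan gives no figure for this point, so there is none to reproduce. The check sets the sections side by side and then adds up scheduled minutes.

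**Content listed in this article**

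| Content | Residential | Outpatient |
|---|---|---|
| Exercise, manual therapy, education, home programme | Yes | Yes |
| Hydrotherapy | Group 1 description; Table 2 | None listed |
| Occupational therapy with CBT, relaxation, coping | Table 2, selected patients | None listed |
| Nutrition | One topic in Table 2; nutritionist in the Interventions text | None listed |

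The sections describing the core components cover exercise, manual therapy, education and the home programme. Hydrotherapy and occupational therapy are outside that list.

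**Residential minutes from Table 2** (sessions × minutes)

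- Group exercise: 12 × 30 to 12 × 45 = 360–540
- Physiotherapy: 5 × 30 = 150
- Hydrotherapy/swimming: 3 × 60 = 180
- Occupational therapy: 3 × 60 = 180
- Education: 2 × 60 = 120
- Total with occupational therapy: 990–1170 (25 sessions)
- Total without: 810–990 (22 sessions)

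Share = minutes in modalities listed for this arm only ÷ total scheduled minutes.

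- Referred patient: (180 + 180)/1170 = 31% to 360/990 = 36%
- Patient not referred: 180/990 = 18% to 180/810 = 22%

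**Same numerators on the Procedure section's schedule.** Seven sessions a day over 5 days is 7 × 5 = 35 sessions of 30–60 min, or 35 × 30 = 1050 to 35 × 60 = 2100 min. This does not agree with the 25 sessions in Table 2. Keeping 35 sessions for every patient:

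- Referred patient: 360/2100 = 17% to 360/1050 = 34%
- Patient not referred: 180/2100 = 9% to 180/1050 = 17%

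**Outpatient minutes**

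- Procedure section: 2 × 45 + 6 × 30 = 270 to 2 × 60 + 6 × 30 = 300
- Table 3: 2 × 45 + 6 × 30 = 270 to 2 × 60 + 6 × 40 = 360
- Minutes listed for hydrotherapy or occupational therapy: none

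**Overlap.** Much of the hydrotherapy row is strengthening, range-of-motion and aerobic work done in water. Swimming is also an option in the shared aerobic component. Pain management and coping with daily living are in the shared Education section. The shares above are therefore upper limits for content that is distinct in kind.

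**The case against.** A reader might infer that the trial cannot answer its stated question. The documents do not support that. The purpose, primary aim, primary hypothesis and design all compare a residential multidisciplinary intervention with outpatient care. That is a comparison of packages, and randomisation can answer it. The statement of the primary aim needs no change.

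It can also be said that the disputed sentence is read too strictly. It does not say that only structure and process differ. The same paragraph discloses group versus individual format, team versus physiotherapist delivery, and different amounts of contact. The Background describes residential care as psychosocially broader, and the Interventions section says programme design will differ under shared goals. This stands for setting, format, staffing and contact time, which are declared. It does not cover added modalities: a disclosed difference in amount is not a disclosed difference in kind, and the list of examples in the sentence does not alter its claim that content is the same.

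A reader might also take 31–36% against zero as the measured amount of distinct content. That goes too far. The overlap above lowers it, occupational therapy is for selected patients, and the Procedure section's own schedule gives smaller shares. Nutrition is a thin point: it is one item in Table 2, and none of the four residential education topics named in Table 3 is nutrition.

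Finally, full content is referred to Additional file 1, which is not shown and could list more for outpatients. Silence in Table 3's outpatient column is weak evidence alone, since its residential column does not name hydrotherapy either. The correct wording is that no counterpart is listed in this article. The Group 1 and Group 2 descriptions still differ directly, and the sections conflict as written.

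**Conclusion.** The point holds in limited form. The article claims equal therapeutic content, and its own arm descriptions and Table 2 contradict it. Attributing a difference to structure, process or setting with content held constant is therefore unsupported.

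The modalities listed for the residential arm only take at most 31–36% of scheduled time for patients referred to occupational therapy and 18–22% for others on Table 2, or 17–34% and 9–17% on the 35-session schedule. These figures assume that every listed session takes place and count all hydrotherapy as distinct, which overstates it. They also rest on this article without the intervention guide.

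The randomised comparison of packages, its error rate and its power are not affected. The defect lies in what may be concluded.

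**What to change.** 1. Reconcile the Group 1 and Group 2 descriptions, the equal-content sentence in the Procedure section, the team list in the Interventions text and Table 2. The Group 1 team list omits the nutritionist named in the Interventions text, and the session counts (35 against 25) disagree. Which content and schedule are right is for the investigators.
2. Replace the equal-content sentence with a statement that goals and core components are shared, while the residential arm has additional modalities, named there.
3. In the Procedure section and the Discussion, state that the contrast is between whole packages and that no effect will be attributed to residential delivery, structure or process alone.
4. Optionally, report the modalities each participant received beside the primary result. The article mentions patient timetables but not attendance, so this may need a simple attendance record. It would describe what was delivered; it would not separate the effects.

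Items 1 to 3 cost wording only and leave treatment, sample size and analysis as they are. The price is a narrower conclusion.

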### Randomisation and treatment allocation concealment

A block randomisation method will be used to randomise subjects into groups that result in equal sample sizes. This method will ensure a balance in sample size across both groups over time. Blocks are small and balanced with pre-determined group assignments, which keeps the numbers of subjects in each group similar at all times, whilst ensuring there is a 50:50 likelihood of participants being allocated to either group. Due to the possible influence of gender on the efficacy of strengthening exercise [32, 33], the study will only recruit male participants. After patient eligibility has been confirmed and informed consent obtained, a sealed envelope will be opened to reveal group allocation by an independent administrator not involved in the recruitment, treatment or assessment of study outcomes. A plain language statement will inform participants that they have an equal chance of receiving the residential MDT or individualised outpatient intervention. Group allocation will be documented and communicated to the supervising therapists by the independent administrator. Prior to the study, all treating staff will have received a briefing on the study protocol, the ethical, clinical and scientific basis of the study, the randomisation process and specific intervention for each treatment group, in line with the study protocol. It is not possible, relevant or necessary to blind participants to treatment allocation in this study. The clinical staff supervising both groups will be, by necessity, unblinded. Day and Altman [34] suggest blinding assessment by using non-involved assessors to record outcome scores. This is not possible in our study as independent assessors with specific knowledge of quantification of clinical outcomes are not available due to specialist staff man-power limitations. To minimise the potential influence of outcome assessors, instructions are standardised to ensure consistency in measurement. A medical statistician assisting with statistical analysis will be blind to group allocation until completion of the analysis.

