### Outcome measures

Outcome measures with proven validity and reliability have been selected based on those recommended for clinical trials of intra-articular FAI [53], and current practice in UK military rehabilitation [54]. Standardised instruments recommended by OMERACT-OARSI guidelines [55] will also be included. These guidelines require measures of pain, physical function and a global assessment of health related quality of life. Participants will be assessed at baseline, on completion of treatment (1-week MDT group; 6-weeks IP group) and 12-weeks follow up (Fig. 1). The follow-up time-frames are the same for both groups (12-weeks), and all participants will be assessed at baseline and 12-weeks on the same clinical outcome measures. The inclusion of post-treatment measures may help reveal if any differences occur as a consequence of the different interventions (e.g., the immediate post-treatment scores by group). All outcome measures will be conducted, administered and overseen by the same supervising therapist on each occasion. Outcome measures used in the study are summarised in Table 4.

**Table 4 Tab4:** Summary of outcome measures

Primary outcome measure^a^	Data collection instrument
Function in daily living	Subscale of HAGOS
Physical function, activity level	Subscale of HAGOS
Hip symptoms, numeric pain rating	Subscale of HAGOS, subscale of NAHS, VAS
Secondary outcome measures^a^	
General health status	EuroQol -5D (EQ-5D-3 L)
Mood, anxiety, depression	HADS
Objective functional performance	6-minute walk test
Hip range of motion	Clinical methods and goniometry
Dynamic balance/postural control	Modified Star Excursion (Y-Balance) Test
Hip muscle strength	Hand held dynamometry
Treatment efficacy & self efficacy	SIRBS
Adherence to home-based exercise	Training Diary and 11-point rating scale
Patient demographics & past treatment	Questionnaire

^a^The primary end-point for data analysis is 3-months. All measures will be taken at baseline, post-treatment (1-week MDT group; 6-weeks IP group), 3-months with the exception of patient demographics which will only be assessed at baseline

*HAGOS* Copenhagen Hip and Groin Outcome Score, *NAHS* non-arthritic hip score, *VAS* visual analogue scale, *HADS* hospital anxiety and depression scale, *SIRBS* sports injury rehabilitation beliefs survey

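### Baseline self-reports are taken after participants know their group, and an unblinded supervising therapist administers the self-reported primary outcomes

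*Protocol article*

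**What the plan says.** The order of events is spread over three sections of the protocol article.

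- **Randomisation and treatment allocation concealment:** "After patient eligibility has been confirmed and informed consent obtained, a sealed envelope will be opened to reveal group allocation". A completed baseline assessment is not named as a condition. The same section adds: "Group allocation will be documented and communicated to the supervising therapists by the independent administrator".
- **Procedure (text after Fig. 1):** "Patients agreeing to participate will be informed of treatment group assignment and referral arrangements by a civilian member of the clinical team". Later in the same paragraph: "Baseline testing will be conducted immediately prior to commencement of treatment".
- **Interventions, Table 3:** Day 1 of the residential programme is "Admission MDT clinic and baseline measures". For the outpatient arm, a footnote says that the time allotted to Session 1 excludes baseline measures, which implies that they are taken around that session.

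On who collects the data, Outcome measures says: "All outcome measures will be conducted, administered and overseen by the same supervising therapist on each occasion". On blinding, the randomisation section says: "The clinical staff supervising both groups will be, by necessity, unblinded". It explains the absence of independent assessors as follows: "This is not possible in our study as independent assessors with specific knowledge of quantification of clinical outcomes are not available", attributing this to limits on specialist manpower. The mitigation offered is standardised instructions.

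Sample size defines the primary endpoint as change from baseline to 12 weeks in the HAGOS daily-living subscale and VAS pain. Statistical analysis calculates differences from baseline and describes a repeated-measures model with treatment and time as factors. It states no baseline covariate.

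**The concern.** In an open trial, the one self-report that can be kept free of knowledge of the allocation is the baseline. Here it is not. A participant who is pleased or disappointed with his group may rate his hip differently from how he would have rated it before the envelope was opened. If that reaction differs between arms, it enters the change score as though it were a treatment effect.

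The second part concerns administration. The reason given for having no independent assessors is a lack of people skilled in quantifying clinical outcomes. That may fit dynamometry or inclinometry. It does not fit a questionnaire or a 100 mm line that the participant marks himself. Even so, the supervising therapist, who knows the allocation, administers these too.

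The Design section and the Discussion disclose the lack of blinding and possible assessor bias. Neither mentions the timing of baseline.

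**Working it through.** **Order of events.** Eligibility and consent, then envelope opened, then participant told his group and therapists told the allocation, then attendance for treatment, then baseline. In the residential arm baseline falls on the admission day, when the allocation is self-evident. The three sections agree, and nothing in the article puts a questionnaire before the envelope.

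**How a baseline shift enters the estimate.** Let b be the between-arm difference in how far knowledge of allocation moves the mean baseline score. Assume that the shift is confined to baseline.

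- Change score: each arm's mean change moves by minus its own baseline shift, so the contrast is biased by b in absolute size.
- Baseline-adjusted analysis: the slope on baseline is about the baseline–outcome correlation r when the SDs are equal, so the bias is about r × b.

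If an identical shift persisted at 12 weeks, it would cancel in the change score. The documents do not say which pattern to expect.

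**Inputs.** From Sample size: target difference 5.2 points, SD 11, two-sided alpha 0.05, 43 per group. Assumed, because the documents give no value: b = 1, 2 or 3 points; r = 0.5, with a range of 0.3 to 0.7; SD 11 at each visit. With r = 0.5 the SD of change is 11 × √(2 × 0.5) = 11, so both analyses use the stated SD.

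**The plan's own figure.** The stated 43 per group does not follow from its inputs: 2 × (1.96 + 0.8416)² × 11² / 5.2² = 70.2, so 71 per group (72 by the t-test). That is a separate matter. Here 43 serves only as the planned number analysed per arm.

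**Calculation.** For the change score, SE = 11 × √(2/43) = 2.372. For the adjusted analysis at r = 0.5, SE = 2.372 × √(1 − 0.25) = 2.054. The false-positive rate when there is no true effect is P(|Z + bias/SE| > 1.96).

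| Assumed b | Change-score bias, share of 5.2 | False-positive rate | Adjusted bias (r = 0.5), share of 5.2 | False-positive rate |
|---|---|---|---|---|
| 0 | 0 | 5.0% | 0 | 5.0% |
| 1 | 1.0, 19% | 7.1% | 0.5, 10% | 5.7% |
| 2 | 2.0, 38% | 13.5% | 1.0, 19% | 7.8% |
| 3 | 3.0, 58% | 24.4% | 1.5, 29% | 11.3% |

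For b = 2 and r from 0.3 to 0.7, the adjusted bias is 0.6 to 1.4 points and the false-positive rate 5.8% to 13.1%. A baseline taken before allocation is known sets b to zero. A shift in the 12-week answers alone would enter either analysis in full and is unaffected by when baseline is taken.

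**The case against.** The best counter-argument is that measuring just before treatment is a reasonable choice. The article counts the 12 weeks from the start of treatment, the VAS asks about the past 24 hours, and HAGOS was chosen partly for sensitivity to weekly change. A score from the assessment clinic would be older by an interval that is not given and that could differ between a residential course and outpatient appointments. The article also does not say that trial consent is completed at that clinic. These points stand. They make the remedy a trade-off and are the reason to keep the pre-treatment set.

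Much of the unblinded-assessment issue is already disclosed, and participants cannot be blinded. That too stands: only the baseline timing and the therapist's handling of self-completed forms are new here.

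A reader might infer more than the documents support:

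- *That bias has been shown.* The documents give neither its size nor its direction. The 1 to 3 points are an illustration.
- *That analysis cannot help.* Baseline adjustment reduces a baseline-only shift, as the table shows.
- *That each participant hands his form to his own therapist.* The article says supervising therapist. These therapists know the allocation and receive the guidelines for tailoring treatment, so involvement in treatment is a fair reading. Who is in the room, or sees the scores, is not stated.
- *That the remedy is free, or that the independent administrator could collect the forms.* No staffing figures are given, and the protocol keeps that person out of outcome assessment.
- *That an earlier baseline would rescue the intention-to-treat set.* Someone who leaves before treatment would probably lack 12-week data as well, and no rate of such withdrawal is given.

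**Conclusion.** The point holds as a design weakness that should be corrected. The article's own sequence makes baseline HAGOS, NAHS and VAS post-allocation, unblinded self-reports, and the protocol neither defends nor acknowledges this. The stated reason for unblinded assessment does not reach self-completed forms.

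The size is unknown. If a differential shift occurs and is confined to baseline, it passes in full into an unadjusted change contrast and in part, by about the correlation, into an adjusted one. The illustrative percentages rest on the assumed shifts and correlations, on reading 11 as the SD, and on 43 analysed per arm. Confidence is high about the order of events and limited about how much it matters. The baseline component can be avoided; the 12-week component can only be reduced.

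**What to change.** 1. Have participants complete HAGOS, NAHS, VAS and the other questionnaires themselves, after consent and before the envelope is opened, for example at the multidisciplinary injury assessment clinic that all attend before randomisation. Make completion a condition for opening the envelope.
2. Use this set as the baseline in the primary analysis. Keep the pre-treatment set for a sensitivity analysis.
3. Record the interval from the pre-allocation questionnaires to treatment start and report it by arm.
4. At every visit have questionnaires completed in private and returned sealed, with the treating therapist neither present nor shown the scores. The independent randomisation administrator should not handle them. A study administrator is a possible collector, but the article does not show that one attends visits, so this must be arranged. Objective tests can stay with the therapists.
5. Add to the limitations that 12-week self-reports remain open to knowledge of allocation.

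The cost is a short form-filling slot, some handling of forms, and a baseline that is older when treatment starts by an interval the document does not give and that may differ by arm.
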